#### The weekly frequency of defecation

The frequency of bowel movements during the week before each visit will be assessed at baseline and 2, 4, 6 and 8 weeks after randomisation. A normal defecation is defined as a daily stool frequency ≤3 times and a stool consistency of type (like a sausage or snake; smooth and soft).^24^

#### Work and Social Adjustment Scale

The Work and Social Adjustment Scale (WSAS) will be assessed at baseline and weeks 2, 4, 6 and 8 using a five-domain scale with a total possible score of 40, with each item scoring from 0 (not affected) to 8 (severely affected). The scale is used to measure problems in functioning with work, home management, social activities, private leisure activities, and family and relationships.^25^

#### IBS-Quality of Life

The IBS-Quality of Life (IBS-QOL) questionnaire consists of 34 items; each item includes a five-point response scale and is a valid and reliable instrument to establish changes in health-related QOL of patients with IBS.^26^ Patients themselves will be required to complete the questionnaire at baseline and weeks 2 and 4 after the treatment. Then, the total scores of each item will be calculated and analysed, with higher scores suggestive of better QOL.

#### Self-Rating Anxiety Scale and Self-Rating Depression Scale

The majority of patients with IBS have comorbid anxiety and/or depression, which are in turn strongly associated with symptom severity.^27 28^ Hence, anxiety and depression symptoms will be assessed at baseline and weeks 2 and 4 using the Self-Rating Anxiety Scale (SAS) and Self-Rating Depression Scale (SDS). It is noteworthy that SDS >56 will be excluded before the first treatment because of an unstable psychological state or accompanying psychological disorders. According to statistical standards, the total score is multiplied by 1.25 and is then converted into a standardised score ranging from 25 to 100. For SAS, grades 1, 2 and 3 are related to scores of 53–62, 63–72 and >72, respectively.^29^ For SDS, grades 1, 2 and 3 correspond to scores of 50–60, 61–70 and >70, respectively.^30^ Higher scores indicate more severe anxiety and depression.

### Blinding assessment

To test the patient-blinding effects, all patients will be asked to guess whether they have received acupuncture or sham acupuncture at the end of the first treatment session and the 12th treatment session.

### Safety evaluation

In this trial, AEs will be monitored during the 4 weeks of treatment and the next 4 weeks of follow-up. Any adverse reactions that occurred during the study will be recorded. Common side effects of acupuncture or sham acupuncture include (but are not limited to) subcutaneous haematoma, local bleeding, skin bruising, needle site itching, continuous needle site pain, muscle spasm and dizziness. In the event of a serious AE, the necessary measures will be taken immediately for the safety of the subject. The time of occurrence, severity, duration, outcome and treatment-related status will be reported to the Medical Ethics Committee within 24 hours.

### Sample size and statistical analysis

Based on two sample size mean literature data speculation and previous clinical experience,^12 31^ we anticipate the scores of two acupuncture groups on the continuation of current medications as follows: responders can improve refractory IBS on the IBS-SSS with scores of 30 and 15, respectively. The SD is set at 15, and the ratio between the acupuncture and sham acupuncture groups is 1:1. The sample size is calculated with a 20% type II error rate (80% power) and 5% type I error. The superiority trial will be adopted to minimise the difference between the two groups, and a 10-point is expected. In total, a sample size of 154 (77 patients in each group) is estimated. Allowing for 10% loss to follow-up, the sample size expands to 85 patients in each group.

All analyses will be performed using the intent-to-treat (ITT) and the per-protocol (PP) populations. ITT requires all participants to receive a baseline assessment of the primary outcome and at least one acupuncture session or one sham acupuncture administration. Missing values will be imputed through the multiple imputation method. The PP population is usually defined as patients who complete at least 80% of the treatment protocol without major protocol violations. The primary outcome will be assessed using analysis of covariance and adjusted for baseline total IBS-SSS. For other secondary outcomes, continuous variables will be analysed using Student’s t-test or the Wilcoxon rank-sum test, and data will be represented as the mean±SD or median; categorical variables will be calculated using Fisher’s exact test or the Wilcoxon rank-sum test, and data will be presented as frequencies (percentages). In terms of efficacy factors, other covariates, such as age, sex, disease duration, conventional pharmacological agent classification and so on, will be considered for further revision. The differences in blinding and AEs between the groups will be compared using the χ^2^ test. Moreover, we have decided to carry out a subgroup analysis based on patients with IBS subtypes, avoiding a heterogeneous patient population that may affect the efficacy results.

Statistical analysis of all data in this study will be performed by a specialised third-party statistician evaluation. SAS, V.8.2 statistical software (SAS Institute), will be used for data analysis. A two-sided p<0.05 will be considered statistically significant.

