## Outcomes

### Primary outcome

#### IBS Symptom Severity Score

According to previous assessment recommendations,^21^ the IBS Symptom Severity Score (IBS-SSS) is a validated scoring system that relates to the severity of abdominal pain (IBS-SSS1), frequency of abdominal pain (IBS-SSS2), bloating (IBS-SSS3), satisfaction with bowel habits (IBS-SSS4) and disruption of QOL (IBS-SSS5), and will be used as the primary outcome of this trial. Participants will respond to each question on a 100-point Visual Analogue Scale. Each of the five questions generates a maximum score of 100 points, and the total is scored from 0 to 500, with higher scores indicating severe symptoms: normal (<75), mild IBS (75–175), moderate IBS (175–300) and severe IBS (>300). IBS-SSS will be assessed at baseline and 2, 4, 6 and 8 weeks after randomisation.

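### The planning SD of 15 is implausibly small for a 0–500 IBS-SSS total and its type is not stated, so the claimed 80% power is unsupported, above all for a 10-point difference

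*Protocol article*

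**What the plan says.** The protocol article defines the primary outcome under IBS Symptom Severity Score: "Each of the five questions generates a maximum score of 100 points, and the total is scored from 0 to 500". The severity bands there run from 75 to 175 (mild), 175 to 300 (moderate) and above 300 (severe).

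The section Sample size and statistical analysis takes its inputs from cited literature and clinical experience. It expects that "responders can improve refractory IBS on the IBS-SSS with scores of 30 and 15, respectively", and then: "The SD is set at 15, and the ratio between the acupuncture and sham acupuncture groups is 1:1". It adds: "The superiority trial will be adopted to minimise the difference between the two groups, and a 10-point is expected". The error rates are given as "The sample size is calculated with a 20% type II error rate (80% power) and 5% type I error", and the same section says "A two-sided p<0.05 will be considered statistically significant". The result is 77 per group (154 in all), raised to 85 per group for 10% loss. The primary analysis is an analysis of covariance adjusted for baseline total IBS-SSS.

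Boxes 1 and 2 set no limit on the IBS-SSS total. The only severity element is in the Discussion: the literature-based description of refractory IBS, which clinicians use to preselect patients, includes a floor of 30 mm on the pain component.

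**The concern.** Power depends on the difference divided by the SD, so the SD carries the whole calculation. Fifteen points is 3% of a 500-point scale. About 95% of values would lie within 2 × 1.96 × 15 = 59 points, less than half the width of the moderate band. Entry is not restricted by total score, and the article's own list of limitations says that differences in symptom severity must be taken into account.

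If the true spread is larger, the trial has less power than the article claims, and a non-significant result would say less about acupuncture than readers would assume. Two gaps make this hard to judge from the text: the type of SD is not stated, and the 10-point figure could be either the target difference or a superiority margin.

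**Working it through.** **Inputs.** From the article: five items of 0–100, total 0–500; expected improvements of 30 and 15 (difference 15); SD 15; a 10-point figure of unclear meaning; 80% power; two-sided 5%; 77 per group. SDs other than 15 and all baseline correlations below are assumptions, because the article gives none.

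**1. The stated sample size.** n per group = 2(1.960 + 0.842)² × 15² / Δ² = 3532 / Δ².
- Δ = 15: 15.7, so 16 (17 with the t distribution).
- Δ = 10: 35.3, so 36 (37 with t).
- Δ = 5, that is 15 less a 10-point margin: 141.3, so 142 (143 with t).

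None gives 77, and one-sided tests (13, 28 and 112) do not either. With SD 15, 77 per group would give over 99.9% power for 15 points, 98% for 10 and 54% for an effective 5.

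**2. What SD 15 implies for the items.** For five items with equal SD s and common correlation ρ, SD of total = s√(5 + 20ρ). Setting this to 15 gives s = 15/√5 = 6.7 if the items are independent, 4.5 at ρ = 0.3, and 15/5 = 3.0 if they are fully correlated.

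**3. A benchmark from the article's own bands.** An even spread over 175–300 has SD 125/√12 = 36.1, before any mild or severe patient is counted.

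**4. Could 15 be a change or residual SD?**
- Residual SD = SD√(1 − r²). Reaching 15 needs r = √(1 − (15/36.1)²) = 0.91 from a total SD of 36, or 0.95 from 50.
- Change SD = SD√(2(1 − r)). Reaching 15 from 36.1 needs r = 1 − 225/(2 × 1302) = 0.91.

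**5. Power at 77 per group.** With a noncentral t on 152 degrees of freedom, 80% power needs Δ/SD of at least 0.4544. The break-even effective SD is therefore 10/0.4544 = 22.0 for 10 points and 15/0.4544 = 33.0 for 15 points. The detectable difference is 0.4544 × SD.

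| Effective SD | Power, 15 points | Power, 10 points | Detectable at 80% |
|---|---|---|---|
| 15 (stated) | >99.9% | 98% | 6.8 |
| 30 | 87% | 54% | 13.6 |
| 36 | 73% | 40% | 16.4 |
| 50 | 46% | 23% | 22.7 |
| 75 | 23% | 13% | 34.1 |

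**6. With the planned baseline adjustment.**

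| Total SD | r | Residual SD | Power, 15 points | Power, 10 points |
|---|---|---|---|---|
| 36 | 0.5 | 31.2 | 84% | about 50% |
| 50 | 0.5 | 43.3 | 57% | 30% |
| 50 | 0.8 | 30.0 | 87% | 54% |
| 75 | 0.5 | 65.0 | 30% | 16% |

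For 10 points to keep 80% power (residual 22), r would have to be √(1 − (22/36.1)²) = 0.79 at a total SD of 36, or 0.90 at 50.

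**The case against.** The strongest reply is that the design does not need SD 15 to be true. Since 77 per group is well above what SD 15 requires for 10 or 15 points, there is slack: 15 points keeps 80% power up to an effective SD of 33. At a total SD of 36 with a modest baseline correlation of 0.5, power for 15 points is 84%. This stands. A reader might infer that differences of 10 to 15 points are largely undetectable in this trial. The documents do not support that in general. It follows only if the effective SD is about 50 or more, and no passage shows that it is.

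A reader might also take severity to be wholly unrestricted. That too goes too far, because the preselection description has the 30 mm pain floor and Box 1 requires long-standing symptoms and failed treatments. But a floor on one item of five, with no ceiling and no limit on the total, does not bring the SD of the total near 15.

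Third, the inputs rest on cited sources that are not at hand, and they are worded as improvements, so 15 may be a change SD. This is a fair reason to ask for its type and source. It does not rescue the value, which would still need a correlation of about 0.91 or more between self-reported scores weeks apart.

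Finally, a non-significant result still comes with a confidence interval, which can rule out larger effects. This is true, and it is a reason to state the detectable difference correctly.

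**Conclusion.** The concern holds in this form. An SD of 15 is not credible for the IBS-SSS total as the article defines it, and the stated 80% power does not follow from the stated inputs on any reading of the difference. The size of the loss cannot be fixed from the documents. With 77 per group, 80% power is kept only up to an effective SD of about 22 for 10 points or 33 for 15 points. The 15-point difference stays detectable in favourable cases; the 10-point difference probably does not. If the 10 points are a superiority margin, the effective difference is 5 and power is 54% even at SD 15.

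This rests on a two-sided 5% test, equal groups of 77, and assumed SDs and correlations. The SD of 36 illustrates an even spread over one band and is not an estimate for this population.

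**What to change.** In Sample size and statistical analysis:

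1. State whether the SD is that of the total, the change or the covariance-adjusted residual, and name its source.
2. Replace 15 with an SD of that type on the 0–500 scale, taken from the cited data.
3. State whether 10 points is the target difference or a superiority margin, and how it relates to the improvements of 30 and 15.
4. Keep the planned 170 patients, and restate the power and the detectable difference for that number in place of the present derivation of 77.
5. If no source SD can be found, print the range in the working above and label the SDs as assumptions.

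The cost is protocol wording. No patients are added, and the article says the trial is still in preparation. The downside is that the stated sensitivity of the trial becomes less favourable.

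### The planned 77 patients per group at 80% power cannot be reproduced from the stated inputs, and the role of the 10-point figure is not defined

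*Protocol article*

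**What the plan says.** All the planning figures stand in the Protocol article, section Sample size and statistical analysis.

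- Anticipated improvement in the acupuncture and sham groups: "responders can improve refractory IBS on the IBS-SSS with scores of 30 and 15, respectively".
- Variability and allocation: "The SD is set at 15", and "the ratio between the acupuncture and sham acupuncture groups is 1:1".
- Error rates: "The sample size is calculated with a 20% type II error rate (80% power) and 5% type I error".
- The 10 points: "The superiority trial will be adopted to minimise the difference between the two groups, and a 10-point is expected". No noun follows the figure, so the text does not say what the 10 points are.
- Result: "In total, a sample size of 154 (77 patients in each group) is estimated".
- Loss: "Allowing for 10% loss to follow-up, the sample size expands to 85 patients in each group". This gives the 170 patients named in the Abstract.

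The same section plans an analysis of covariance of the primary outcome, adjusted for baseline total IBS-SSS, and sets the criterion: "A two-sided p<0.05 will be considered statistically significant". It mentions no margin in the analysis and gives no baseline correlation.

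**The concern.** The paragraph prints a full set of inputs and an output, so the output can be checked without any outside source. It does not follow from the inputs.

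The 10-point figure makes the problem worse, because neither natural meaning fits its surroundings. As the difference expected between the groups, it contradicts improvements of 30 and 15, which differ by 15. As a superiority margin, it has no counterpart in the planned analysis.

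The 80% power is the stated justification for enrolling 170 patients. The two meanings put the error in opposite directions. In one, the trial is several times larger than its inputs require. In the other, it falls well short of 80%.

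**Working it through.** **Inputs (all from the section cited).** SD = 15; 1:1 allocation; power 80% (z = 0.8416); type I error 5%. The sample-size sentence gives no sidedness. The analysis is two-sided (z = 1.9600), and one-sided 5% (z = 1.6449) is shown as a variant. Candidate differences d are 15 (30 − 15), 10 (the 10-point figure), and 5 (15 − 10, if the 10 is a margin).

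**Attempt to reproduce 77.** Per group, n = 2 (z_α + z_β)² (SD/d)².

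Two-sided, (1.9600 + 0.8416)² = 7.849:
- d = 15: 2 × 7.849 × 1 = 15.7, so 16 (17 with the t-test).
- d = 10: 2 × 7.849 × 2.25 = 35.3, so 36 (37 with the t-test).
- d = 5: 2 × 7.849 × 9 = 141.3, so 142 (143 with the t-test).

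One-sided 5%, (1.6449 + 0.8416)² = 6.183: 13, 28 and 112 by the same formula (14, 29 and 112 with the t-test).

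None is near 77. Other variants also fail under the stated error rates:
- SD multiplied by √2 with d = 10 gives 71.
- Reading 30 and 15 as response percentages gives 121 two-sided or 95 one-sided.
- Adjusting for Wilcoxon efficiency (0.955 or 0.864) gives at most 20 for d = 15 and 43 for d = 10, and at least 118 for d = 5.

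**Power that 77 per group delivers.** SE = 15 × √(2/77) = 2.417; power ≈ Φ(d/SE − z_α).

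| Reading | d/SE | Two-sided 5% | One-sided 5% |
|---|---|---|---|
| Difference 15 against zero | 6.20 | >99.9% | >99.9% |
| Difference 10 against zero | 4.14 | 98.5% (t: 98.4%) | 99.4% (t: 99.3%) |
| Difference 15 over a margin of 10 | 2.07 | 54.3% (t: 53.8%) | 66.4% (t: 66.1%) |

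**What 77 per group would fit.** At SD 15 the difference detectable with 80% power, two-sided, is 2.8016 × 2.417 = 6.8 points (6.0 one-sided). Alternatively, 80% power would need an SD of 22.2 for a difference of 10, or 33.2 for a difference of 15. The protocol states none of these.

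**Effect of the ANCOVA.** Adjusting for baseline reduces residual variance, so for differences of 10 or 15 it lowers the required n and widens the gap from 77. Under the margin reading, 77 would suffice if the variance fell by 1 − 77/141.3 = 45.5%, a baseline correlation of about 0.67 (about 0.56 one-sided). No correlation is given.

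**A possible origin, not stated anywhere.** With d = 5, one-sided 5% and 90% power, n = 154.15 per group. The printed total of 154 would then be a per-group number taken as a total. That needs 90% power where the text says 80%, and a one-sided test where the analysis is two-sided. It is conjecture and does not settle what was intended.

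**The case against.** The strongest reply is that the declared test is clear and well powered. A baseline-adjusted ANCOVA at two-sided 5% with no margin tests against zero, and 77 per group is more than enough for 10 or 15 points at SD 15. This stands, and it limits the point to a wrong justification rather than a shortage of patients under the planned test.

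Several stronger readings are tempting but not supported:

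- A reader might infer that the trial has only about even odds of success. The 54% holds only if a 10-point margin was intended. The text never uses the word margin, and the planned analysis would not test one.
- A reader might infer that a significant result could not be interpreted. The declared test settles that: significance rejects zero difference. The ambiguity lies in the planning paragraph.
- A reader might conclude that 80% is impossible on any assumptions. A baseline correlation of about 0.67 would restore it under the margin reading. Because none is stated, the accurate claim is that 77 is not reproducible from the inputs given.
- A reader might take the word responders to mean a calculation in responders only. The same passage speaks of means and group scores and gives an SD, so loose wording for group mean improvements is more likely.
- A reader might call the loss step an error. Dividing gives 77/0.9 = 85.6, so 86, while multiplying gives 77 × 1.1 = 84.7, so 85. The gap is one patient per group and a matter of convention.

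**Conclusion.** The point holds as a failure of reproducibility joined to an undefined quantity. From the stated SD, error rates and differences, the required size is about 17, 37 or 142 to 143 per group (two-sided, t-test or normal approximation), against a stated 77. Under the test the protocol plans, the stated 80% power understates what 77 per group delivers for the differences named, and 80% corresponds to about 6.8 points.

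This rests on three assumptions: that 15 is the SD of the analysed score, that 30 and 15 are group mean improvements, and that no variance reduction from the baseline adjustment was built in. The last can only raise the power for 10 or 15 points. Underpowering is conditional on a margin reading that the document neither states nor excludes.

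**What to change.** Rewrite the sample-size paragraph around one hypothesis.

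- State that superiority is tested against zero, as the planned ANCOVA implies, and give the sidedness in the same sentence.
- Label the 10 points as the planning difference or remove them, and reconcile the result with 30 versus 15.
- Give the SD actually used and, if a baseline correlation was assumed, its value.
- Keep 170 patients, and replace the 80% with what about 77 evaluable per group delivers: at SD 15, about 98% power for 10 points or over 99.9% for 15. Equivalently, state a minimum detectable difference of about 6.8 points at 80% power.

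This costs one paragraph and no extra patients.

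If the sponsor did intend a 10-point margin, the cost is larger. The analysis must then test against that margin, and the power must be restated as about 54% two-sided (66% one-sided) at 77 per group. Keeping 80% on that reading would take about 142 evaluable per group, or 142/0.9 = 158 per group with 10% loss.

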### Interventions

To ensure the safety and proper operation of acupuncture, all acupuncturists will participate in the standard operation process (SOP) of skin disinfection, location of acupoints and non-acupoints, fundamental puncture and needle manipulations before the trials. Treatments will be performed by licenced acupuncturists who have at least 3 years of experience in acupuncture. Acupuncture will be discontinued if the patients experience any adverse events (AEs) after acupuncture. The schedule of enrolment, interventions, assessments and participant visits is shown in figure 2.

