### Acupuncture group

Patients allocated to the acupuncture group with disposable and sterile acupuncture needles (length: 25–40 mm, diameter: 0.30 mm; Hwatuo, Suzhou, China) will receive treatment with acupuncture three times a week for 4 weeks for a total of 12 treatment sessions. Based on traditional Chinese medicine (TCM) theory and our clinical experience, the prespecified acupoints used here will include bilateral *Tianshu (ST25)*, *Shangjuxu (ST37)*, *Zusanli (ST36)* and *Neiguan (PC6*) (table 2 and figure 3). The exact location and depth of needling for each point will be determined based on the 2006 People’s Republic of China National Standard: The Name and Location of Acupoints (GB/T 12346-2006).^19^ After insertion, manipulations of twirling, lifting and uniform reinforcing-reducing manipulation will be performed on all needles to elicit ‘deqi’. The compositional sensation of ‘deqi’ includes numbness, soreness, distention, aching and heaviness, which are believed to be an essential component for acupuncture efficacy.^20^ Then, the needles will be removed after a 30 min session with clean cotton balls to prevent bleeding.

**Table 2 T2:** Locations of acupoints in the acupuncture group

Acupoints		Locations
Tianshu (ST25)	Bilateral	On the same level of the umbilicus, and 2 cun* lateral to the anterior midline
Shangjuxu (ST37)	Bilateral	6 cun directly below Dubi (ST35), and one finger-breadth lateral to the anterior border of the tibia
Zusanli (ST36)	Bilateral	3 cun directly below Dubi (ST35), and one finger-breadth lateral to the anterior border of the tibia
Neiguan (PC6)	Bilateral	On the line joining Daling (PC7) and Quze (PC3), between the tendons of palmaris longus and flexor carpi radialis, 2 cun above the transverse crease of the wrist

*1 cun (≈20 mm) is defined as the width of the interphalangeal joint of patient’s thumb.

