### Sham acupuncture group

The participants in the sham acupuncture group will also receive the same treatment duration and frequency of sessions as the real acupuncture group. Similarly, sham acupuncture will be performed at predefined bilateral sites (non-acupoints 1–4) not corresponding to acupuncture group traditional points or meridians, penetrating to the same depth but without needle manipulation for ‘deqi’ (table 3 and figure 3). Patients will be informed of the two types of acupuncture as follows: ‘in this trial, different types of acupuncture will be compared, but another approach might not target your additional symptoms.’ This language will be used to avoid deception while unifying the simulation conditions of the two groups as much as possible, mixing real and sham points, and this might enhance patient compliance.

**Table 3 T3:** Locations of non-acupoints in the sham acupuncture group

Non-acupoints		Locations
Non-acupoint 1	Bilateral	In the middle of Daheng (SP15) and Zhangmen (LR13) points (lateral aspect)
Non-acupoint 2	Bilateral	In the medial arm on the anterior border of the insertion of the deltoid muscle at the junction of the deltoid and biceps muscles
Non-acupoint 3	Bilateral	On the same level 1–2 cun* outboard lateral of the ST36
Non-acupoint 4	Bilateral	In the middle of the medial epicondyle of the humerus and the styloid process of ulna

*1 cun (≈20 mm) is defined as the width of the interphalangeal joint of patient’s thumb.

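### As written, adverse events are also compared in the per-protocol set, and if an adverse event ends the course, that set drops patients because of the outcome being compared

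*Protocol article*

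**What the plan says.** Under Sample size and statistical analysis, the protocol article sets one rule for every analysis: "All analyses will be performed using the intent-to-treat (ITT) and the per-protocol (PP) populations". Later in that paragraph it adds: "The differences in blinding and AEs between the groups will be compared using the χ^2^ test". That sentence names no population of its own, so on its face it falls under the general rule.

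The two sets are described in the same place. For ITT: "ITT requires all participants to receive a baseline assessment of the primary outcome and at least one acupuncture session or one sham acupuncture administration". For PP: "The PP population is usually defined as patients who complete at least 80% of the treatment protocol without major protocol violations".

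The Interventions section states: "Acupuncture will be discontinued if the patients experience any adverse events (AEs) after acupuncture". It gives no threshold of severity or relatedness, and does not say whether the session or the whole course ends.

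The acupuncture arm is treated "three times a week for 4 weeks for a total of 12 treatment sessions", and sham patients "will also receive the same treatment duration and frequency of sessions as the real acupuncture group". The Safety evaluation section monitors AEs over the 4 treatment weeks and the 4 follow-up weeks.

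**The concern.** A PP set is meant to be selected on adherence. Here, if an AE ends the course, adherence is itself decided by the AE. A patient with an early AE cannot reach 80% of treatment, so the PP set keeps patients who had no AE, or had one only late in the course or in follow-up. A between-group AE test in that set is selected on its own outcome.

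The direction of the bias is predictable: AE proportions in PP come out too low in both arms. If the arms truly differ, the arm with more AEs loses more patients and the difference tends to shrink. A true difference is plausible, because needles are manipulated to elicit deqi in one arm and not in the other. The Abstract gives efficacy and safety together as the aim, so a PP safety table that looks reassuring by construction could mislead.

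**Working it through.** The article states no AE rate, no timing of AEs and no expected PP size, so there is no figure of the plan to reproduce. The check takes the stated rules and shows a range for what is not stated.

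**Inputs from the protocol article**
- Planned sessions: 12 in each arm (Acupuncture group; Sham acupuncture group).
- PP threshold: at least 80% of treatment (Sample size and statistical analysis).
- Discontinuation after any AE (Interventions).
- Patients per arm: 85 (Sample size and statistical analysis).
- AE monitoring: 4 weeks of treatment plus 4 weeks of follow-up (Safety evaluation).

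**Assumptions**
- Treatment completion is counted in sessions.
- Discontinuation ends the course.
- The risk of a first AE per session, h, is constant. It is varied from near 0 to 10%.
- No other reason removes patients from PP.

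**Step 1: the PP cut-off.** 0.80 × 12 = 9.6, so 10 sessions are needed. Stopping after session 9 gives 9/12 = 75%, which is out. Stopping after session 10 gives 10/12 = 83%, which is in. A first AE after any of sessions 1 to 9 therefore removes the patient from PP.

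**Step 2: share of patients with an on-treatment AE who are removed.** Share = [1 − (1 − h)^9] / [1 − (1 − h)^12].

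| h per session | Any AE over 12 sessions | Share removed from PP | AE proportion seen in PP |
|---|---|---|---|
| near 0 | near 0 | 75.0% | near 0 |
| 0.5% | 5.8% | 75.6% | 1.5% |
| 1% | 11.4% | 76.1% | 3.0% |
| 2% | 21.5% | 77.2% | 5.9% |
| 5% | 46.0% | 80.4% | 14.3% |
| 10% | 71.8% | 85.4% | 27.1% |

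The last column is 1 − (1 − h)^3, because only first AEs at sessions 10 to 12 stay in PP. In terms of the true on-treatment proportion c, it is 1 − (1 − c)^(3/12):
- c = 30%: 1 − 0.70^0.25 = 8.5%
- c = 10%: 1 − 0.90^0.25 = 2.6%

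**Step 3: allow for first AEs in follow-up.** Let f be the share of AE patients whose first AE comes after treatment, and spread on-treatment first AEs evenly over the 12 sessions. Share removed = 0.75 × (1 − f).

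| f | Share of all AE patients removed |
|---|---|
| 0 | 75% |
| 10% | 67.5% |
| 20% | 60% |
| one third | 50% |
| 50% | 37.5% |

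More than half are removed only while f is below about one third.

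**Step 4: effect on the comparison, as an illustration.** Assume per-session risks of 3% and 1% in the two arms, on-treatment AEs only, and a two-sided 5% test of two proportions.
- All 85 treated per arm: 1 − 0.97^12 = 30.6% against 1 − 0.99^12 = 11.4%. The difference is 19.3 points (from unrounded values) and power is about 88%.
- PP: 85 × 0.97^9 ≈ 65 patients against 85 × 0.99^9 ≈ 78. AE proportions are 1 − 0.97^3 = 8.7% against 1 − 0.99^3 = 3.0%. The difference is 5.8 points (from unrounded values) and power is about 33%.

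**The case against.** The strongest reply is that the plan already contains a suitable comparison. ITT requires at least one real or sham session, so it is close to a treated set and keeps every patient who stops for an AE. A low PP figure would stand beside an ITT figure that shows the events. This stands, and it confines the damage to the PP comparison.

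A reader might go further and call the ITT set unfit for safety because it also requires a baseline IBS-SSS. The documents do not support that. The Primary outcome section schedules IBS-SSS at baseline, and nothing suggests that patients will be needled without it.

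A second reply is that the word discontinued may refer only to the session. The Safety evaluation section lists bruising, local bleeding and needle-site itching among common side effects, so ending the course for each of them is not the only possible reading. This also stands: on that reading, only patients who do not resume and so fall short of 80% are lost.

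Third, a reader might infer that most patients with an AE will be removed. The article gives no AE rate or timing. The listed side effects are largely needle-related, which makes AEs during treatment likely, but that is an inference. The cut-off of 10 of 12 sessions is inferred too, since the PP definition speaks of 80% of the treatment protocol and is introduced as what is usual.

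Finally, a safety set may be defined in a full protocol or SAP that is not shown, so its absence from the article is not the point. What remains is a positive statement that covers all analyses and is followed by an AE test. A SAP that took AEs out of PP would contradict that sentence.

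**Conclusion.** The point holds in a conditional form. As written, the AE comparison is made in the PP set as well as in ITT. If discontinuation means the end of the course and completion is counted in sessions, PP membership depends on the AE outcome. The PP AE proportions are then biased low, and a true difference between arms tends to shrink.

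The direction follows from the stated rules under that reading, while the size rests on assumption: between the 75% to 85% of Step 2 and the 37.5% at the lower end of Step 3, and less again if only the session is stopped. The primary outcome is untouched, and the ITT comparison of AEs is not materially affected. The change is still worth making, because safety is part of the stated aim and the PP result could be misread as reassurance.

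**What to change.** In Sample size and statistical analysis, limit the general rule to efficacy analyses. Add that AEs are summarised and compared in all patients who received at least one real or sham session, by treatment received and whatever the number of sessions completed, and that no AE comparison is made in the PP set.

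Reconcile the Interventions section with the PP definition: say whether discontinuation refers to the session or the course, and how a patient who stops for an AE is counted towards the 80%. This takes no view on the stopping rule itself.

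The cost is a sentence or two of text and no new data. Reported AE rates may look less favourable than the PP figures would have.
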